## Abstract

**Background:**

The clinical inability to correctly identify late fetal growth restriction (FGR) within a group of fetuses who are identified as small for gestational age (SGA) is an everyday problem for all obstetrician-gynecologists. This leads to substantial overtreatment of healthy small fetuses but also inadequate detection of the growth-restricted fetuses that may benefit from timely delivery. Redistribution of the fetal circulation, signaled by an abnormal ratio of the Doppler velocity flow profiles of the umbilical artery and the middle cerebral artery, more specifically an increased umbilicocerebral ratio (UCR) (or its inverse: a decreased cerebroplacental ratio (CPR)), is an adaptation to chronic hypoxemia and nutritional scarcity with long-term consequences in survivors. The relevance of an abnormal UCR has been signaled extensively, and there is a general consensus that it is a signal of FGR, independent of size, with a strong association with poor outcomes. Yet, in the current literature, no comparisons of a monitoring-delivery strategy based on unfavorable UCR have been published. The objective of the Doppler Ratio In fetal Growth restriction Intervention Trial At (near) Term (DRIGITAT) is to evaluate if the timing of the delivery based on an abnormal UCR in late preterm fetuses identified as SGA improves neurodevelopmental outcomes at 2 years of age.

**Methods:**

The DRIGITAT study is a national multicenter cohort study of women with singleton pregnancies between 32 and 37 weeks of gestation identified as SGA, with a nested randomized controlled trial (RCT) in case of an abnormal UCR (> 0.8). Recruiting centers are in The Netherlands. In the nested RCT, women are randomized to either immediate induction of labor or expectant management from 34 weeks in case of severely abnormal size (EFW or FAC < p3) and from 36 weeks in case of mildly abnormal size (EFW or FAC p3–p10). The primary outcome measure is the 7-point average difference in the composite cognitive score (CCS) and composite motor score (CMS) on the Bayley-3 at 2 years. Secondary outcome measures include a composite outcome of neonatal morbidity, perinatal mortality, mode of delivery, maternal quality of life, costs, and predictive value of serum biomarkers. Analyses will be by intention to treat. The required sample size is determined for the nested RCT as 185 patients.

**Discussion:**

This study will provide insight into the diagnostic efficacy of UCR measurement in the evaluation of SGA fetuses in order to differentiate the healthy SGA fetus from the growth-restricted fetus and to determine if a fetus with abnormal UCR benefits from early delivery.

**Trial registration:**

Healthcare Evaluation Netherlands NTR6663. Registered on 14 August 2017.

## Administrative information

Note: The numbers in curly brackets in this protocol refer to SPIRIT checklist item numbers. The order of the items has been modified to group similar items (see http://www.equator-network.org/reporting-guidelines/spirit-2013-statement-defining-standard-protocol-items-for-clinical-trials/).

## Introduction

### Background and rationale {6a}

Fetal growth restriction (FGR) is traditionally defined as small for gestational age (SGA), a definition based on size, usually below the 10th percentile on growth reference centiles, and thus by definition affects 10% of all fetuses. SGA however indicates a reference-based *small-sized* fetus, and FGR indicates a fetus smaller than its intrinsic growth capacity, which may not be below the 10th percentile on the reference curve [1]. Among SGA fetuses is a considerable group of fetuses that is constitutionally small but healthy and among the appropriate for gestational age (AGA) fetuses is a group of fetuses that are growth restricted despite an apparently normal weight.

The pathophysiological mechanism in FGR is often uteroplacental insufficiency, with multiple underlying causes, leading to the failure of the placental exchange unit to serve fetal needs. When the growth-restricted fetus remains undelivered, the insufficiency progresses and the prolonged placental restraints put the fetus at risk for fetal demise [2]. Also, while remaining in utero, permanent alterations in fetal physiology increases the fetus’ risks of disease in adulthood [3]. When delivered timely, usually in the late preterm period, the baby is at risk for neonatal transitional disease and gross morbidity.

Because of the diagnostic substitution of SGA with FGR, the effect of any approach is diluted by the inability to identify fetuses with true placental growth restriction that may benefit from timely interventions by avoiding fetal risks that surpass the neonatal disadvantages [4]. A major challenge is to differentiate the FGR fetus from the healthy fetus within the group of SGA fetuses. The other challenge, outside the scope of this trial, is to identify the growth-restricted fetus within the group of apparent normal size fetuses.

Functional parameters, such as Doppler ultrasound and serum biomarkers, can help distinguish the FGR fetuses from healthy SGA fetuses. Redistribution of the fetal circulation, signaled by an increased umbilicocerebral ratio (UCR) or its inverse a reduced cerebroplacental ratio (CPR), caused by a decrease in resistance in the middle cerebral artery (MCA, reflecting cerebral flow) and an increased resistance in the umbilical artery (UmbA, reflecting placental flow), is an adaptation to scarcity with long-term adverse consequences in survivors [5–11]. Serum biomarkers, including soluble fms-like tyrosine kinase-1 (sFlt-1) and placental growth factor (PlGF), have received attention as markers for placental function [12, 13], as they have a considerable association with relevant outcomes [14, 15].

There are also clear associations of late prematurity, a possible consequence of timed delivery, with significant adverse neurodevelopmental outcomes. Even in the absence of severe neonatal morbidity, which is uncommon in late prematurity, there are significant effects from preterm delivery, predominantly transitional disease (neonatal jaundice, hypoglycemia) that are temporary but may have a bearing on long-term neurodevelopmental outcomes [16]. These may be related to a simple effect from gestational age, but are more likely due to the underlying reason for preterm delivery.

The dilemma is obvious: previous studies clearly show some diagnostic accuracy of the UCR resulting in many (doctors) to believe in an “obvious” effective test-treatment combination in SGA fetuses [11, 17]. Intuitively, physicians balance the effect on outcomes from cohort evidence of associations of the diagnostic tools with the cohort evidence of the effect of gestational age. In this process, the fear of the worst outcome (stillbirth), despite its low incidence, often drives decisions towards early interventions with a high risk of mild morbidity, also for the long term. The above leads to practice variation due to different perceptions of risk. However, prospective comparative evidence is lacking. There is international consensus that a RCT on intervention on abnormal UCR is now opportune, including the investigation of serum biomarkers for their potential added value in guiding timing of delivery.

We hypothesize that with the addition of the UCR measurement in evaluation of SGA fetuses, we are better able to differentiate the SGA fetus at risk from the healthy SGA fetus. Furthermore, by directing intervention towards timely delivery based on an abnormal UCR, we hypothesize that (1) a higher number of growth-restricted fetuses are no longer exposed to prolonged risks of placental insufficiency and are delivered timely with better neurodevelopmental outcomes and (2) less fetuses that are SGA and physiologically small are subjected to unnecessary interventions; all the above leading to improved health outcomes and saved costs.

### Objectives {7}

The objective of this study is to use the diagnostic efficacy of the UCR in pregnant women with fetuses identified as SGA to differentiate those fetuses who are subject to risks related to placental insufficiency and thus growth restricted and those fetuses who are not at increased risk and thus healthy. Subsequently, this identification will be used for time delivery.

The research aims of the DRIGITAT study are as follows:To investigate if, in a cohort of late preterm SGA fetuses, timely delivery in a nested RCT in case of an abnormal UCR improves immediate perinatal outcome and long-term neurodevelopmental outcome as tested with Bayley-3 at 2 years (hypothesis testing)To assess the predictive value of serum biomarkers, for the primary outcome and other main secondary outcomes (hypothesis generating)To estimate the costs and cost-effectiveness of the above monitoring intervention strategy, with potentially shifting the majority of fetuses to more expectant management and a minority towards earlier induction of delivery

### Trial design {8}

The trial design is a cohort study of SGA pregnancies with a nested randomized controlled trial in fetuses with an abnormal UCR, superiority design.

## Methods: participants, interventions, and outcomes

### Study setting {9}

The DRIGITAT is a nationwide trial conducted in secondary and tertiary care hospitals in The Netherlands that evaluate and manage (late) fetal growth restriction. The trial is embedded in the Dutch Obstetric Consortium, a collaboration of obstetrics hospitals in The Netherlands. A list of current study sites can be obtained at www.zorgevaluatienederland.nl/DRIGITAT.

### Eligibility criteria {10}

In order to be eligible for inclusion in the observational cohort, a patient must meet all of the following criteria:Singleton pregnancyGestational age from 32 + 0 up to and 36 + 6 weeksIdentified SGA (estimated fetal weight (EFW) or fetal abdominal circumference (FAC) below the 10th percentile)

In order to be eligible to participate in the nested RCT, a patient must meet all of the above-described criteria and additional following criteria:Abnormal UCR of more than 0.8 (equals a CPR of less than 1.25) on at least 2 occasions with an interval of at least 1 workday (minimum of 15 h)

Two groups can be included in the RCT, dependent on FGR severity.EFW and/or FAC < p3 AND gestational age from 34 + 0 up to and including 36 + 6 weeks of gestationEFW and/or FAC < p10 AND gestational age from 36 + 0 up to and including 36 + 6 weeks of gestation

The EFW for inclusion or randomization should be calculated with the Hadlock 3 formula (including the FAC, head circumference (HC) and femur length (FL) [18], and the percentile value of the EFW should be based on the Hadlock reference curve [19].

The percentile value of the FAC should be based on the Verburg reference curve [20].

#### Exclusion criteria

A potential patient who meets any of the following criteria will be excluded from participation in this study (both the cohort and RCT):Maternal age < 18 yearsInability to give informed consent (lack of comprehension, language)Uncertainty about the estimated due dateSuspicion of congenital anomalies which can influence the prognosis of the pregnancy or health of the fetusProven chromosomal abnormalitiesMaternal or fetal indication for short-term delivery

### Who will take informed consent? {26a}

A trained and authorized member of de local study team will counsel the patient and take informed consent.

### Additional consent provisions for collection and use of participant data and biological specimens {26b}

Additional consent will be obtained to store residual material in a biobank for 50 years. This concerns the remaining blood after biomarker analysis of the maternal blood sample that is taken from all participants. This consent can also be used to store placental tissue or other residual material collected during standard care. Consent is also obtained to contact participants for additional follow-up investigation that does not fall within the initial research question of this study.

### Interventions

#### Explanation for the choice of comparators {6b}

Concerning the hypothesis that a healthy SGA fetus has normal Doppler measurements and the FGR fetus has abnormal Doppler measurements as a reflection of redistribution to compensate for hypoxia by prioritizing the brain for oxygenated blood, the best solution would be to end the unfavorable intra uterine condition and to deliver the fetus with an insufficient placenta. The disadvantage is relative preterm birth that not only ends starvation and hypoxia but also ends maturation of the fetus. When the growth-restricted fetus remains undelivered, the progressive insufficiency puts the fetus at risk for fetal demise. Also, while remaining in utero, permanent alterations in fetal physiology increases the fetus’ chances of disease in adulthood. On the other hand, when delivered timely, usually in the late preterm period, the baby is at risk for neonatal transitional disease and gross morbidity. When a small fetus has normal Dopplers it is considered to be a healthy SGA fetus and delivery can be awaited.

#### Intervention description {11a}

Delivery from 34 weeks onwards when UCR is abnormal and fetal size is severely abnormal (EFW or FAC below p3), and delivery from 36 weeks when UCR is abnormal and fetal size is mildly abnormal (EFW or FAC p3–p10). Delivery has to be pursued as soon as possible from the moment of randomization.

#### Criteria for discontinuing or modifying allocated interventions {11b}

Safety criteria have been established for discontinuing the allocated intervention in case of expectant management. Guidance and safety criteria are given regarding the timing of the delivery in the cohort and in the expectant arm of the RCT. Delivery is indicated when:Cardiotocography (CTG) suggests fetal distressDoppler ultrasound of the umbilical artery suggests very high antenatal risks:Reversed end-diastolic flow (REDF) in the UmbA on two occasions with at least 1 day in between from a gestational age of more than 32 weeksAbsent end-diastolic flow (AEDF) in the UmbA on two occasions with at least 1 day in between from a gestational age of more than 34 weeksPulsatility index (PI) in the UmbA above the 95th percentile on two occasions with at least one day in between from a gestational age of more than 37 weeksEFW or FAC below the 10th percentile from a gestational age of 38 weeks in the expectant arm of the RCT or refusal to participate in the RCTEFW or FAC below the 3rd percentile from a gestational age of 38 weeks in the cohortEFW or FAC below the 10th percentile from a gestational age of 40 weeks in the cohortA non-reassuring CTG tracePresence of other clinical signs indicating short-term delivery according to standard protocol, such as severe pre-eclampsia or repeated episodes of reduced fetal movements

In case of allocation to immediate delivery, there are no criteria for discontinuing the intervention other than participant request. When a woman is not willing to be randomized for the timing of the delivery, she will be followed up for intention-to-treat analysis and will receive usual care and timing of delivery.

#### Strategies to improve adherence to interventions {11c}

Standard phrases to use in the electric patient files for the guidance of monitoring and management have been made available. The research team is approachable 24/7 for any relevant questions. The adherence to the allocated intervention is monitored by the study monitor through the electronic database where time and indication of delivery are recorded in the case report form.

#### Relevant concomitant care permitted or prohibited during the trial {11d}

The DRIGITAT protocol allows centers to provide their usual care according to local protocol. All other care deemed clinically necessary is allowed. The minimum required procedures and assessments that participants must undergo are described below. Most of these procedures and assessments are already embedded in local protocols on FGR of participating hospitals.Cardiotocography: CTG monitoring takes place in all fetuses with an abnormal UCR with a frequency as indicated by local protocol. The study protocol advises CTG monitoring at least twice a week in case of abnormal UCR.Ultrasound investigation: the study protocol recommends to perform a weekly ultrasound scan on all participants. The ultrasounds will be performed by trained personnel.Fetal biometry: routine fetal biometry measurements according to the departmental protocol should take place every 10–14 days.Fetal and maternal Doppler measurements: fetal Doppler measurements should be done on a weekly basis. At each visit, multiple Doppler measurements are taken, and the measurement of best quality is used. This is usually the PI of the lowest value. When the UCR is > 0.8 for the first time, Doppler measurements should be repeated to confirm the abnormal UCR. Ideally, the measurement is repeated the next day, with a minimum interval of 15 h. Randomization can take place when the UCR is abnormal on two different occasions with at least one day (a minimum of 15 h) in between.Middle cerebral artery (MCA) Doppler measurement: Doppler blood flow waveforms should be measured in the middle cerebral artery just past the level of the bifurcation of the internal carotid artery [21].Umbilical artery (UmbA) Doppler measurement: Doppler blood flow velocity waveforms should be measured in the umbilical artery in a free-floating loop of the mid-section of the umbilical cord [22].Uterine artery (UtA): Doppler blood flow waveforms should be measured in the uterine artery, ideally 1 cm downstream from the crossover point with the external iliac artery [23].Amniotic fluid measurements: amniotic fluid index (AFI) or the single deepest vertical amniotic fluid pocket (SDP) should be measured.Maternal surveillance: standard maternal surveillance will include, at least, the measurement of blood pressure and, if abnormal, a check for proteinuria.Placental pathology: we advise all hospitals to send the placenta to their own pathology department for histopathologic investigation according to national consensus protocol [24].

#### Provisions for post-trial care {30}

The sponsor has a liability insurance which is in accordance with article 7 of the Dutch medical research involving human subjects act (WMO). The sponsor (also) has an insurance which is in accordance with the legal requirements in the Netherlands (Article 7 WMO and the Measure regarding Compulsory Insurance for Clinical Research in Humans of 23 June 2003). This insurance provides cover for harm to participants through injury or death caused by the study. This insurance applies to harm that becomes apparent during the study or within 4 years after the end of the study.

### Outcomes {12}

#### Primary outcome

The primary outcome includes neurodevelopmental outcomes at 2 years of age in all children born in the RCT and in a subset of children born in the cohort. The neurodevelopmental score will be assessed by means of the Bayley-III test [25].

The Bayley Scales of Infant and Toddler Development (Bayley-III is the current version) is a standard series of measurements to assess the development of infants and toddlers, ages 1–42 months. This measure consists of a series of developmental play tasks and takes between 45 and 60 min to administer and derives a developmental quotient (DQ) rather than an intelligence quotient (IQ). Raw scores of successfully completed items are converted to scale scores and to composite scores.

The developmental score is derived separately for the cognitive and motor domain with a mean of 100 and SD of 15. Higher scores indicate a better level of development. A 7-point difference (− 0.5 SD) between the two treatment groups in this trial is considered to represent a meaningful difference. Women who were eligible for the RCT but did not want to be randomized for intervention will also be asked to participate in the follow-up with Bayley-III testing.

#### Secondary outcomes

In all participants (RCT and cohort), the following outcomes will be analyzed:Short-term perinatal morbidity, defined as a composite outcome of level of neonatal care, intravenous antibiotics treatment more than 3 days, any respiratory support, any cerebral damage, cranial ultrasound, neonatal jaundice, neonatal hypoglycemia, and its individual components. These are relatively mild outcomes since neonatal morbidity in near-term deliveries is uncommon, while differences in primary outcomes are likely significant.Perinatal mortality.Mode of delivery.Maternal quality of life through the European Quality of life 5-Dimension 5-Level (EQ5D-5L) Questionnaire, 6 weeks, 12 months, and 24 months after delivery.Pediatric development using the Ages & Stages Questionnaire, Third Edition (ASQ-3) and the Child Behavioural Checklist for ages 1.5–5 (CBCL/1.5-5) 24 months after delivery.◦Language development, derived from the ASQ-3 subscale communicationChild growth through questionnaires of height, weight, and head circumference at 12 and 24 months after delivery.Child symptoms of asthma, rhinitis, and eczema through a modified version of the ISAAC Questionnaire 24 months after delivery.Questionnaire on the duration of (exclusive) breastfeeding at 12 months after delivery.Predictive value of serum biomarkers (PlGF, sFlt) on the fetal outcome and fetal and placental size.

In RCT, participants and a control group from the cohort the following outcomes will be analyzed at 24 months after delivery:Resource use through a modified version of the iPCQ and iMCQ at 24 months after delivery in the RCT and a matched control group from the cohortWeight and height, BMI, head circumference, and blood pressure

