## Statistical methods

### Statistical methods for primary and secondary outcomes {20a}

Principal analyses will be performed on an intention-to-treat basis. The primary analysis will compare mean Bayley-III scores at 2 years and test the difference using a linear regression model controlling for the stratification factor. If women with suspected FGR (UCR > 0.8 or CPR < 1.25) allocated to the intervention group (timely delivery) have toddlers with better Bayley scores at 2 years, it will be concluded that timely delivery is beneficial based on UCR classification.

A sample of children born in the cohort will also be invited for Bailey-III testing and other outcomes assessed at 2 years of age. A sampling of patients from the cohort will be done against the index date of the trial patient.

Secondary endpoints will be analyzed as relative risks or differences in means with 95% confidence intervals. The chi-square tests and *t*-tests will be used for parametric dichotomous and continuous outcomes respectively. The Mann-Whitney tests with a median difference in medians (Hodges-Lehmann estimate) will be used for non-parametric continuous outcomes.

Data on pregnancy and short-term outcomes are expected only to be missing if patients withdraw consent. Long-term outcomes are anticipated to be missing in up to 15% of patients. The primary outcome will be assessed on a complete case analysis, with sensitivity analysis using multiple imputation.

An alpha of 0.05 is considered for statistical significance.

Data from the cohort study will be used as a comparator group to evaluate the course of all pregnancies, irrespective of UCR/CPR value, and inform whether different UCR/CPR thresholds or combination with other (serum) markers should be considered.

Statistical analyses will be conducted using the latest version of SPSS (SPSS Chicago, IL, USA).

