Health-related quality of life will be measured using the EQ5D-5L Questionnaire provided to women who have entered the trial at baseline, 6 weeks, 12 months, and 24 months after delivery. In the case of missing data on either costs or effects, these will be imputed by using multiple imputation techniques. The prevalence of any relevant outcomes in neonates will be extracted from CRF registration forms and electronic health records at the end of the trial. The utility scores related to these outcomes will be derived from relevant scientific literature for the calculation of cost-effectiveness. After completion of data collection, the incremental cost-effectiveness ratio (ICER) will be calculated by dividing the difference in costs between usual care and the intervention by the difference in QALYs between usual care and intervention. ICERs will be calculated for mothers and children separately and combined to analyze the potential differences in cost-effectiveness. Sensitivity analysis will be performed on parameters, which are expected to have the largest uncertainty. Bootstrapping will be used to determine the uncertainty surrounding the ICERs. The results from the bootstrap analysis will be used for plotting a cost-effectiveness acceptability curve to demonstrate the probability that the intervention strategy will be cost-effective compared to current practice when using a range of cost-effectiveness thresholds. Cost-effectiveness planes will be created to graphically represent the results from the bootstrap analysis.

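### The cost-effectiveness section plans a baseline EQ-5D-5L that the outcomes section does not list, and the stated secondary analysis leaves it unused, at some cost in precision

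*Protocol article*

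**What the plan says.** Three places in the protocol article bear on maternal EQ-5D-5L.

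- **Secondary outcomes.** Under the lead-in "In all participants (RCT and cohort), the following outcomes will be analyzed", the entry is "Maternal quality of life through the European Quality of life 5-Dimension 5-Level (EQ5D-5L) Questionnaire, 6 weeks, 12 months, and 24 months after delivery". No baseline is listed.
- **Cost-effectiveness analysis (CEA).** The questionnaire is "provided to women who have entered the trial at baseline, 6 weeks, 12 months, and 24 months after delivery". The incremental cost-effectiveness ratio divides the cost difference "by the difference in QALYs between usual care and intervention". The section does not say how maternal QALYs are built.
- **Statistical methods {20a}.** "Secondary endpoints will be analyzed as relative risks or differences in means with 95% confidence intervals". The tests named are chi-square and t-tests, which "will be used for parametric dichotomous and continuous outcomes respectively", with Mann-Whitney and Hodges-Lehmann where a non-parametric method is wanted. No covariate is named. The primary outcome is treated differently: the plan will "test the difference using a linear regression model controlling for the stratification factor".

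**The concern.** One instrument has two descriptions. They disagree on whether there is a baseline and on who completes the questionnaire: everyone in the RCT and cohort, or women who entered the trial. The second difference matters because the CEA draws on the RCT and a matched subgroup of the cohort. If the trial here means the RCT only, the matched cohort women have no baseline utility. Any comparison with them is not randomised, so a missing baseline would then affect confounding as well as precision.

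The analysis question follows from the schedule. If baseline EQ-5D-5L is collected, a comparison of follow-up scores that ignores it discards information already paid for. This is not a detail left open for an analysis plan. The article names an unadjusted method for continuous secondary endpoints, directly after naming an adjusted one for the primary. At stake is the width of the confidence interval for maternal quality of life.

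**Working it through.** **1. The two schedules side by side**

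| | Secondary outcomes | CEA |
|---|---|---|
| Baseline | not listed | listed |
| Post-delivery times | 6 weeks, 12 and 24 months | the same three |
| Population | RCT and cohort | women who entered the trial |

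The post-delivery times agree. Baseline and population do not. The participant timeline (Fig. 1) is not shown, so it cannot settle the matter here.

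**2. The plan's own sample size, for the number analysed**

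Inputs from Sample size {14}: difference 7, SD 15, alpha 0.05 (taken as two-sided), power 80%, loss to follow-up 20%.

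- The two-sample t-test needs 73.05 per arm, so 74 per arm, or 148 analysed.
- 148 / 0.80 = 185 randomised.

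Both stated figures reproduce. They concern the Bayley-III; the article gives no sample-size figure for EQ-5D-5L.

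**3. Cost of leaving baseline out**

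Let r be the correlation between baseline and follow-up EQ-5D-5L. The documents give no value, so r is assumed. In a randomised comparison, linear adjustment for baseline multiplies the variance of the arm difference by 1 − r². The unadjusted variance is therefore larger by 1/(1 − r²).

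The difference detectable with 80% power, in SD units and with 74 per arm, is (1.960 + 0.842) × √(2/74) × √(1 − r²) = 2.802 × 0.1644 × √(1 − r²).

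| Assumed r | 1 − r² | 1/(1 − r²) | Detectable difference (SD) |
|---|---|---|---|
| unadjusted | – | – | 0.461 |
| 0.3 | 0.91 | 1.10 | 0.439 |
| 0.5 | 0.75 | 1.33 | 0.399 |
| 0.6 | 0.64 | 1.56 | 0.368 |

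In terms of variance, the unadjusted analysis would need about 10%, 33% or 56% more women to match the adjusted one. If the Mann-Whitney route is taken, these factors are only a guide.

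**4. Bias**

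There is none between randomised arms. Randomisation makes the expected baseline difference zero, and the confidence interval of the unadjusted comparison already allows for chance imbalance.

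**The case against.** The strongest reply is that the two sections are compatible. The outcomes section lists times at which an outcome is analysed, and a baseline is not an outcome time. The CEA section may describe a narrower group. An unadjusted randomised comparison is valid, so adjusting a secondary outcome is a choice of efficiency rather than the repair of an error. Much of this stands, and it is why the point is minor. It does not remove the need to say who completes a baseline. Nor does it change the fact that the stated method makes no use of that baseline in the quality-of-life comparison.

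A reader might infer more from these sections. The documents do not support the following readings.

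- *Baseline is not collected.* The CEA section says that it is, and its absence from a list of outcome times does not contradict that.
- *Maternal QALYs can start only 6 weeks after delivery.* The CEA section governs QALYs, and it includes a baseline.
- *Baseline utility is ignored in the QALYs.* The t-test sentence covers secondary endpoints, not the economic analysis. The article is silent on how QALYs are built, and a condensed article may leave that to the full protocol or analysis plan.
- *A chance baseline imbalance would outweigh the effect around delivery.* This sets random error, already in the confidence interval, against a systematic effect. The sizes do not separate either. Assume a utility SD of 0.15 and 92 versus 93 women. One standard error of the baseline difference is then 0.15 × √(1/92 + 1/93) = 0.022. Carried over 2 years at r = 0.3 to 0.5, that is 0.013 to 0.022 QALY. An assumed utility gap of 0.05 to 0.10 over 8 to 10 weeks (2 to 4 weeks before delivery plus the 6 weeks after) gives 0.05 × 8/52 = 0.008 to 0.10 × 10/52 = 0.019 QALY. The ranges overlap.

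**Conclusion.** The point holds in a limited form. The two descriptions of the EQ-5D-5L need reconciling on baseline and population. As written, the secondary analysis does not use a baseline that the CEA section plans to collect. The result is a valid but less precise comparison of maternal quality of life, with variance 10% to 56% higher than necessary for correlations of 0.3 to 0.6. That range rests on an assumed correlation, on linear adjustment, and on baseline being available for most randomised women. Severity is minor, and nothing here shows a fault in the QALY analysis.

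**What to change.** - **Schedule and population.** Use one description in Secondary outcomes and in the CEA section. State whether baseline EQ-5D-5L is completed by RCT women only, by the matched cohort women as well, or by all participants. In RCT women, require it before allocation: the trial is open label, and a self-reported score given after allocation could reflect knowledge of the arm.
- **Analysis.** In Statistical methods {20a}, analyse follow-up EQ-5D-5L in the RCT by linear regression on arm, baseline EQ-5D-5L and the stratification factor as used in the primary model. Report the adjusted mean difference with its 95% confidence interval.
- **Missing baseline.** Fix a simple rule, such as mean baseline or a missing indicator, so that no randomised woman with follow-up is dropped.
- **If maternal QALYs are counted from randomisation,** use the same time horizon in both arms. The 24-month questionnaire is timed from delivery, so running to that visit would give the later-delivered arm more time. At an assumed utility of 0.85, 2 to 4 extra weeks would credit 0.85 × 2/52 = 0.03 to 0.85 × 4/52 = 0.07 QALY for time alone.

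The cost is wording and one covariate. For trial women the baseline questionnaire is already planned; extending it to cohort women would add one form. The small downside is the need for the missing-baseline rule. The sample size and primary analysis stay as they are.
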